## Abstract

**Background:**

Stereotactic arrhythmia radioablation (STAR) is delivered with a planning target volume (PTV) prescription dose of 25 Gy, mostly to the surrounding 75–85% isodose line. This means that the average and maximum dose received by the target is less than 35 Gy, which is the minimum threshold required to create a homogenous transmural fibrosis. Similar to catheter ablation, the primary objective of STAR should be transmural fibrosis to prevent heterogenous intracardiac conduction velocities and the occurrence of sustained ventricular arrhythmias (sVA) caused by reentry. We hypothesize that the current dose prescription used in STAR is inadequate for the long-term prevention of sVA and that a significant increase in dose is necessary to induce transmural scar formation.

**Objective:**

A single arm, multi-center, phase II, dose escalation prospective clinical trial employing the i3 + 3 design is being conducted to examine the safety of a radiation dose-escalation strategy aimed at inducing transmural scar formation. The ultimate objective of this trial is to decrease the likelihood of sVA recurrence in patients at risk.

**Methods:**

Patients with ischemic or non-ischemic cardiomyopathy and recurrent sVA, with an ICD and history of ≥ 1 catheter ablation for sVA will be included. This is a prospective, multicenter, one-arm, dose-escalation trial utilizing the i3 + 3 design, a modified 3 + 3 specifically created to overcome limitations in traditional dose-finding studies. A total of 15 patients will be recruited. The trial aims to escalate the ITV dose from 27.0 Gy to an ITV prescription dose-equivalent level of maximum 35.1 Gy by keeping the PTV prescription dose constant at 25 Gy while increasing the dose to the target (i.e. the VT substrate without PTV margin) by step-wise reduction of the prescribing isodose line (85% down to 65%). The primary outcome of this trial is safety measured by registered radiation associated adverse events (AE) up to 90 days after study intervention including radiation associated serious adverse events graded as at least 4 or 5 according to CTCAE v5, radiation pneumonitis or pericarditis requiring hospitalization and decrease in LVEF ≥ 10% as assessed by echocardiography or cardiac MRI at 90 days after STAR. The sample size was determined assuming an acceptable primary outcome event rate of 20%. Secondary outcomes include sVA burden at 6 months after STAR, time to first sVA recurrence, reduction in appropriate ICD therapies, the need for escalation of antiarrhythmic drugs, non-radiation associated safety and patient reported outcome measures such as SF-36 and EQ5D.

**Discussion:**

DEFT-STAR is an innovative prospective phase II trial that aims to evaluate the optimal radiation dose for STAR in patients with therapy-refractory sVA. The trial has obtained IRB approval and focuses on determining the safe and effective radiation dose to be employed in the STAR procedure.

**Trial registration:**

NCT05594368.

## Background

Cardiovascular diseases account for 32% of deaths globally and 45% of deaths in Europe [1, 2]. Sudden cardiac death (SCD) caused by sustained ventricular tachycardia and fibrillation (VT/VF) account for approximately 50% of these death [3]. The most common causes for VT/VF are ischemic or non-ischemic (i.e. dilated, hypertrophic, etc.) cardiomyopathies (ICM, NIMC) that are associated with myocardial scar formation facilitating the development of arrhythmias.

While implantable cardioverter defibrillators (ICD) reduce the risk SCD due to VT/VF, they do not prevent their occurrence. Therefore, VT/VF remain major cause of morbidity and mortality as well as reduced quality of life in patients with ischemic or non-ischemic cardiomyopathies. Certain antiarrhythmic drugs (in particular amiodarone) and catheter ablation (CA) reduce the rate of VT/VF and SCD [3, 4]. But although CA is efficacious in suppressing sustained monomorphic VT (MMVT) a total recurrence rate of 33.2% was reported in a recent meta-analysis including all randomized controlled trials comparing CA with conservative treatment [5]. Difficulty in reaching arrhythmogenic substrate (intramural or epicardial), large scars and other procedural factors may lead to VT recurrence after an intervention. Additionally, CA can be associated with major complications in up to 9.5% [6].

More recently, stereotactic arrhythmia radioablation (STAR) has been introduced as a non-invasive treatment for refractory sustained MMVT with the delivery of a single fraction high-dose radiotherapy [7–9]. This treatment aims to deliver focal treatment to the arrhythmogenic substrate to ultimately induce transmural fibrosis, similar to the goal of CA.

While initial trials reported a high immediate success rate, a systematic review of the available clinical data found frequent, sustained ventricular arrhythmia (sVA) recurrences after the index procedure in up to 75% of treated patients within the first year. The commonly employed prescription dose has been 25 Gy either homogeneously or inhomogeneously to the 70–85% isodose line and was shown to maintain a high degree of safety [10]. However, from animal experiments, it is evident that such a dose will not be able to induce transmural fibrosis within the myocardium, which is thought to be necessary for long-term success of VT ablation [11]. A probable explanation for these late recurrences may be the lack of such a transmural fibrosis development in the irradiated myocardium. This would be necessary to homogenize the scar to prevent the development of reentry circuits, the cause of MMVT [12]. Indeed, a mechanism alternative to scar homogenization by which STAR may prevent recurrent sVA has recently been proposed [13].

To date, all studies have focused on initial safety and have not yet explored a possible dose-effect relationship for developing transmural fibrosis. In human trials, to date a maximum dose of 25 Gy was prescribed to the target volume, with inhomogeneity allowed in some instances to amount to a maximum point dose of 33 Gy, which is below the anticipated threshold of 35 Gy for transmural scar formation [10, 14]. Pre-clinical trials have yielded similar findings [15]. Increasing the dose to the cardiac target to induce transmural scar formation is a promising approach to increase the long-term efficacy of STAR.

This study hypothesizes that the underlying mechanism of successful VT treatment is the induction of a homogeneous scar formation within the critical arrhythmic substrate for which a higher radiation dose than the currently applied 25 Gy prescription dose will be necessary. Therefore dose-escalation will lead to a significantly reduced long-term VT recurrence rate compared to the currently applied single dose of 25 Gy. This phase II study aims to identify the optimal dose - i.e. minimal efficacious dose required for successful STAR treatment, while not jeopardizing treatment safety.

## Methods

### Study aim

This study aims to demonstrate the safety of escalating the usually employed dose from 25 Gy prescribed to the 65–90% target volume encompassing isodose to a maximum of 32.5 Gy prescribed to the 65–90% with the ultimate goal of decreasing long-term sVA recurrence rates through homogeneous scar formation.

### Study design

DEFT-STAR is an ongoing single arm, multi-center, phase II, dose escalation trial employing the i3 + 3 design. The design has specifically been created for dose finding studies in radiation oncology. This design has been found to be more robust with regard to statistical operating characteristics than the classical 3 + 3 design [16]. After informed consent is obtained from participants, they will be assigned to a radiation dose group according to the dose escalation simulation.

### Sample size calculation

The study is designed as a single arm, multi-center dose escalation trial employing the i3 + 3 design assuming that 15 patients will be treated and an event rate of 20% is acceptable (Fig. 1) [16]. The study will treat 15 patients and escalate the dose up to a maximum level of ITV prescription dose-equivalent level of maximum 35.1 Gy to the 65–90% target encompassing isodose. With the assumption that 15 patients will be treated and a toxicity event rate of 20% ±5 is acceptable, a dose escalation schedule has been simulated [8].

The ITV dose will be escalated from 27.0 Gy to an ITV prescription dose-equivalent level of maximum 35.1 Gy while keeping the PTV prescription dose constant at 25 Gy after each patient if no dose limiting toxicities (DLT) have occurred (E). If a DLT is observed within the first five patients, the dose will not be further increased unless 5 patients were treated at the same dose (S) without occurrence of another DLT in one of these remaining four patients (Fig. 1). In case of a DLT in a second patient at the same dose level a dose de-escalation to the previous lower dose is employed and the current dose will never be used again in this trial (DU). If the ITV prescription dose-equivalent level of maximum 35.1 Gy is reached the remaining patients will be treated at this dose level, until the target cohort of n = 15 is reached. If no radiation associated adverse events occur, dose can be escalated with each recruited patient (i.e. row 0 and columns 1–5 in Fig. 1). The likelihood that dose escalation ensues too quickly with deleterious effects is very small.

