**Fig. 1 Fig1:**
[figure not shown]
Simulation of the dose escalation according to the occurrence of adverse events. Unless an adverse event is registered, dose escalation until the target dose will follow with each patient

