### Ethics and study participant safety

The study has been approved by the Cantonal Ethics Committee of Zurich, Switzerland (BASEC 2022 − 00262). This study will be conducted in compliance with the protocol, the current version of the Declaration of Helsinki, ICH-GCP, as well as all national legal and regulatory requirements. An independent data and safety monitoring board (DSMB) including a board-certified radiation oncologist and cardiologist/electrophysiologist has been established. The DSMC will review and evaluate the accumulated study data for subject safety, study conduct and progress, and make suggestions concerning the continuation, modification, or termination of the study. DSMB meetings will be scheduled before the trial start, after enrollment of the first 2 subjects and another 3 subjects, or at least every 6 months. The trial has been registered at clinicaltrials.gov (NCT05594368).

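### After a second DLT at 35.1 Gy, two consecutive sentences prescribe opposite actions: ban the dose, or treat all remaining patients there

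*Protocol article*

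**What the plan says.** The rules are in the protocol article, Methods, Sample size calculation. In order, they are:

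- Escalate after each patient while no DLT has occurred (E).
- After one DLT, hold the dose until five patients have been treated there, and escalate only "without occurrence of another DLT in one of these remaining four patients" (S).
- After a DLT in a second patient at the same level, "a dose de-escalation to the previous lower dose is employed and the current dose will never be used again in this trial (DU").
- Once the top ITV level of 35.1 Gy is reached, "the remaining patients will be treated at this dose level, until the target cohort of" 15 is complete.

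The ban has no exception for the top level. The fill-up sentence has no condition on DLTs. Study design adds that after consent "they will be assigned to a radiation dose group according to the dose escalation simulation". The matrix is Fig. 1, which is not reproduced in the text at hand. Its legend says that, absent an adverse event, "dose escalation until the target dose will follow with each patient".

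**The concern.** The third and fourth rules both apply when a second DLT occurs at 35.1 Gy. One sends the next patient to 32.4 Gy and closes 35.1 Gy for good. The other keeps that patient and all later ones on 35.1 Gy.

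This is the stopping rule at the highest dose of a trial whose primary outcome is safety. The article does not define DLT separately. If it means the events listed under Outcome measures, these are radiation-associated grade 4 or 5 events, pneumonitis or pericarditis requiring hospitalization, and an LVEF fall of at least 10%. Further sites are being opened (Trial organization and coordination), so investigators who did not write the rule may have to apply it.

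**Working it through.** The article derives no figure on this point that could be reproduced: the 15 patients and the acceptable rate are inputs to a simulation whose scenarios are not given. The check is how often the two sentences collide, and what follows if the fill-up sentence is obeyed.

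**Inputs from the article.** N = 15; four levels (27.0, 29.7, 32.4 and 35.1 Gy, Table 2); the E, S and DU rules above; acceptable event rate 20%.

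**Assumptions.** True DLT rates at levels 1 to 4 are not given, so three sets are used: 10% throughout, 5/10/15/20% and 5/10/20/40%. Each outcome is taken as known before the next patient is assigned. A second DLT at level 1 stops the trial.

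**Step 1: room for the event.** With no DLT in patients 1 to 3, level 4 starts at patient 4, so 15 − 3 = 12 patients can be treated there. The earliest possible second DLT at 35.1 Gy is in patient 5.

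**Step 2: closed form for 12 patients at 35.1 Gy.** P(at least two DLTs) = 1 − (1−p)^12 − 12p(1−p)^11.

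- p = 0.10: 34.1%
- p = 0.15: 55.7%
- p = 0.20: 72.5%
- p = 0.25: 84.2%

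The second DLT falls at patient k on the dose with probability (k−1)p²(1−p)^(k−2). At p = 0.20, k = 12 contributes 4.7 points. A second DLT with someone still to treat therefore has probability of about 72.5 − 4.7 = 67.8%.

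**Step 3: whole trial.** An exact recursion over all 15 patients allows for trials that reach level 4 late or never. The two readings differ only at level 4.

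| Assumed rates, levels 1–4 | Second DLT at 35.1 Gy with patients left | Mean patients at 35.1 Gy after its second DLT, fill-up prevails | Same, ban prevails |
|---|---|---|---|
| 10% at all levels | 24.5% | 1.1 | 0 |
| 5/10/15/20% | 55.8% | 2.9 | 0 |
| 5/10/20/40% | 79.2% | 5.3 | 0 |

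The mean numbers treated at 35.1 Gy agree with this: 9.97 − 7.06 = 2.91 in the second row and 9.44 − 4.12 = 5.32 in the third.

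**Step 4: effect on DLTs.** Mean total DLTs per trial (fill-up against ban) are 2.48 against 2.32 at 5/10/15/20%, a difference of 0.16. At 5/10/20/40% they are 4.39 against 3.24, a difference of 1.15.

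**The case against.** The strongest reply is that the paragraph is sequential. It covers escalation, then holding, then exclusion, and last what to do when no higher level exists. On that reading the fill-up sentence means only that patients stay at 35.1 Gy because there is nowhere to escalate to, and a general default does not cancel a specific safety rule worded with "never". Fig. 1, the cited matrix, may show this. It is missing here only because figures were not extracted, and the article condenses a fuller protocol. The DSMB also meets "after enrollment of the first 2 subjects and another 3 subjects, or at least every 6 months".

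Much of this stands. The ban is the natural reading, and Step 4 shows a small effect on DLTs when the top level is at the acceptable rate. What remains is that the fill-up sentence states an unconditional action that the ban forbids. Fig. 1 could show which was intended, but would not make that sentence right as worded. The last count-based DSMB meeting follows subject 5, the earliest patient who could be the second DLT at 35.1 Gy. Six-monthly reviews continue, but the board can only "make suggestions concerning the continuation, modification, or termination of the study", which does not say which sentence governs.

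Two stronger readings are tempting, and the document does not support them:

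- A reader might infer from the references to five and four patients that the ban covers only the first five at a level, leaving no rule from patient 6 on. Those references belong to the holding rule. The ban sentence speaks of a second patient at the same level and sets no patient limit.
- A reader might object that the ban contradicts the statement that "a toxicity event rate of 20% ±5 is acceptable", since two DLTs in 8 to 11 patients is an observed 25.0% to 18.2%. A count of two that is stricter than the target rate is a legitimate safety choice and needs no correction.

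**Conclusion.** The point holds as a wording conflict in a safety rule, of minor severity. After a second DLT at 35.1 Gy the article prescribes two incompatible actions and gives no priority. The situation is not remote: about 25%, 56% or 79% of trials under the three assumed rate sets. The figures of 1.1, 2.9 and 5.3 patients apply only if the fill-up sentence is taken to override the ban, which is not the likely intention. They also rest on assumed DLT rates and on outcomes being known before the next assignment. The document does not support inferring that the trial intends to continue at a dose it has found too toxic.

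**What to change.** Extend the fill-up sentence with a clause such as: unless the de-escalation rule (DU) is met, in which case the remaining patients are treated at the previous lower dose. Check that Fig. 1 and the full protocol agree.

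The cost is one clause in an amendment, with no extra patients, visits or simulation. The ban after two DLTs at a level can stay as it is.

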### Follow-up

After study intervention, patients will be followed up after one day, one week, and at 3, 6, 9, 12, 18 and 24 months or if any symptoms occur necessitating work-up. Study assessments at the different follow-up timepoints are shown in Table 1.

**Table 1 Tab1:** Planned study assessments during follow-up

Follow-up	D1	W1	M3	M6	M9	M12	M18	M24
**Clinical examination**	X	X	X	X	X	X	X	X
**ECG**	X		X	X	X	X	X	X
**EP Map**	X							
**Lung function**	O			O				
**Chest/Cardiac-CT**	X		X			X		X
**FDG-PET**	O		O		O			O
**SPECT**	O		O		O			O
**MRI**	O		X		X			X
**Transthoracic echocardiography**	X		X		X			X
**ICD readouts**	X	O	X	X	X	X	X	X
**Medication use/dose**	X	X	X	X	X	X	X	X
**Blood samples**	X	O	O		O	O		O
**Chest X-ray**	O		O			O		
**CTCAE v5**	X		X	X	X	X	X	X
**PROMS**	X		X	X	X	X	X	X
**Physician reported QoL**	X		X	X	X	X	X	X

D = day; M = month; O = optional; PROMS = patient reported outcome measures; QoL = quality of life; X = mandatory; W = week. PROMS include EQ5D, SF-36, Treatment decision regret score

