### Outcome measures

The primary outcome of this trial is safety measured by registered radiation associated adverse events (AE) up to 90 days after study intervention. This includes any radiation associated serious adverse event (SAE; at least grade 4 or 5 according to CTCAE v5), in particular death, radiation pneumonitis requiring hospitalization, radiation pericarditis requiring hospitalization and decrease in LVEF ≥ 10% as assessed by echocardiography or cardiac MRI. The secondary outcome measures include efficacy endpoints (i.e. freedom from sustained VT/VF), non-radiation associated safety and patient reported outcome measures (PROMS) as shown in Table 3.

**Table 3 Tab3:** Secondary outcome measures. QOL = quality of life

Efficacy	6-month survival free from electrical storm and incessant VT (binary endpoint) including an initial blanking period of 8 weeks
	Efficacy parameters will be assessed after an initial blanking period of 8 weeks, by comparing the 6 months prior to STAR with the 6 months after treatment, including the 8-week blanking period. All arrhythmic episodes occurring during the blanking period will be collected
	Sustained VT/VF burden as measured by number of post-treatment VT/VF episodes (ECG, ICD readouts). The main analysis will be performed by comparing the 6 months prior to STAR with the 6 months after treatment, which will include an 8-week blanking period
	Time to first sustained VT/VF recurrence as provided by ICD readouts, sustained VT/ICD shock and/or first VT storm
	Reduction of electrical storms and appropriate ATP and ICD shocks
	Need for antiarrhythmic drug use: type and dosages will be collected, and a drug index will be calculated
**Safety**	Overall survival and need for heart transplant or mechanical circulatory support: reported survival and heart transplant rates during follow-up
	Incidence of cardiac arrhythmic mortality or cardiac non arrhythmic mortality
	Non-radiation associated safety, e.g.: Hospitalization for acute heart failure necessitating inotropic therapy and if needed mechanical circulatory support except when other reason is apparent (e.g. acute coronary syndrome) ○ Cardiac tamponade ○ Major stroke or systemic embolism according to current diagnostic standards ○ ICD malfunction necessitating an interventional or operative approach
**Physician-reported and patient-reported QoL**	EQ5D, SF-35, QLQ-5, Treatment decision regret score

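### As published, dose rises with each recruited patient with no completed observation period required, although the only toxicity definition runs to 90 days and no count-based DSMB meeting separates levels 3 and 4

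*Protocol article*

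**What the plan says.** Three statements in the protocol article fix the trigger for escalation.

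- Sample size calculation: the ITV dose goes up "after each patient if no dose limiting toxicities (DLT) have occurred (E" (E is the code for escalate).
- The same section: "If no radiation associated adverse events occur, dose can be escalated with each recruited patient".
- Fig. 1 caption: "Unless an adverse event is registered, dose escalation until the target dose will follow with each patient".

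The section adds an assurance without a figure: "The likelihood that dose escalation ensues too quickly with deleterious effects is very small".

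The DLT is not defined separately. The only toxicity definition is the primary outcome, "registered radiation associated adverse events (AE) up to 90 days after study intervention" (Outcome measures). One component is, in the abstract's words, "decrease in LVEF ≥ 10% as assessed by echocardiography or cardiac MRI at 90 days after STAR".

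Under Follow-up, "patients will be followed up after one day, one week, and at 3, 6, 9, 12, 18 and 24 months", and also whenever symptoms call for work-up. In Table 1, echocardiography and CTCAE grading are marked at day 1 and then at month 3. MRI is optional at day 1 and mandatory at month 3.

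The DSMB meets before the start and then "after enrollment of the first 2 subjects and another 3 subjects, or at least every 6 months" (Ethics and study participant safety). No meeting is tied to the release of a dose level.

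**The concern.** A rule that escalates on the absence of a DLT is only as good as the observation behind that absence. Here the trigger is the next recruitment, while the event may take up to 90 days to appear or be measured. If patients arrive faster than that, no DLT can mean not yet observed.

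The stakes rise at the upper levels. The Background puts the highest point dose in earlier human trials at 33 Gy. Table 2 gives Dmax of 34.5–36.0 Gy at level 3 and 37.5–39.0 Gy at level 4. On the no-DLT path a single patient is treated at level 3, already above that maximum, before level 4 is opened.

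**Working it through.** **No plan figure to reproduce.** The 15 patients are an assumption of the plan, Fig. 1 is not shown, and no figure supports the assurance about speed. An i3+3 table rebuilt with target 0.20 and interval 0.15–0.25 (its exclusion rule is an assumption) gives escalate for 0 of n at every n and stay for 1 of 1 to 1 of 6. This agrees with the text: one event-free patient is enough to go up.

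**Does the 90-day outcome drive escalation?** The abstract says that the sample size rests on an acceptable primary-outcome event rate of 20%. The sample size section uses the same 20% (±5) as the acceptable toxicity rate. The primary outcome runs to 90 days. That the DLT is this outcome is a well-supported inference, not a stated fact.

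**No-DLT path.** Patients 1, 2, 3 and 4 receive levels 1, 2, 3 and 4. The count-based DSMB meetings follow subjects 2 and 2 + 3 = 5. The first can fall before level 3; the second comes after two patients at level 4. None falls between first use of levels 3 and 4, and a six-monthly meeting would do so only if the calendar happened to place it there.

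**Windows completed when patient 4 is treated.** With g days between patients, patient i has been observed for (4 − i) × g days. The number with at least 90 days is none for g below 30, one for 30–44, two for 45–89, and three from 90.

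**Chance that patient 4 receives level 4.** Assume equal spacing, a 90-day DLT rate p_i for patient i, and a share F(t) of those events known by day t:

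P = product over i = 1 to 3 of [1 − p_i × F((4 − i) × g)]

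With uniform onset, F(t) = min(t/90, 1). With full observation and p = 0.20, P = 0.8³ = 0.512. Among trials reaching level 4 at patient 4, the share in which one of patients 1–3 has a DLT that appears only later is 1 − P(full)/P.

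| Spacing | Product, flat 20% | P | Late-DLT share |
|---|---|---|---|
| 60 days | 0.8 × 0.8 × 0.8667 | 0.555 | 0.077 |
| 30 days | 0.8 × 0.8667 × 0.9333 | 0.647 | 0.209 |
| 14 days | 0.9067 × 0.9378 × 0.9689 | 0.824 | 0.378 |
| 90 days or more | 0.8 × 0.8 × 0.8 | 0.512 | 0 |

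**Sensitivity to the rates.** Levels 1–2 resemble doses that the Background calls safe. With assumed rates of 5%, 5% and 20%, full observation gives 0.95 × 0.95 × 0.8 = 0.722. At 60, 30 and 14 days P is 0.782, 0.857 and 0.932, and the late-DLT shares are 0.077, 0.158 and 0.225.

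**Sensitivity to onset, 30-day spacing, flat 20%.** Early-weighted onset, F(t) = 1 − (1 − t/90)², gives a late-DLT share of 0.124. If half the events are seen only at day 90, it is 0.291. If all are found only at the day-90 reading, P is 0.80 at 30-day spacing and 1.00 at 14-day spacing.

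**The case against.** The strongest reply is that this is a condensed article. A DLT definition, its window and a minimum interval between patients are commonly left to the full protocol, which is not shown. The caption can also be read generously: it does not say that the event must already be registered, and the primary outcome uses the same word for events registered up to 90 days. This stands as a limit, since a window may exist. It does not dispose of the point, because the article is not merely silent. It ties each step to the next recruited patient and adds an assurance about speed; the generous reading needs a waiting time that the text nowhere gives.

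Second, a reader might infer that toxicity is invisible until month 3. The documents do not support that. Follow-up allows for symptom-triggered work-up, so deaths and pneumonitis or pericarditis requiring hospitalization would usually surface when they happen. The scenarios with events seen only at day 90 are upper bounds that fit LVEF decline best.

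Third, accrual, onset and level-specific rates are all assumed. At 60-day spacing the excess is about 4 percentage points (0.555 − 0.512 = 0.043). Further sites are only now being opened, so 14-day spacing during the early steps is the least supported case. This stands, and the percentages are illustrations only.

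Fourth, the DSMB has a remit to modify or terminate, and no statement in the article conflicts with its schedule. The gap between levels 3 and 4 is a weakness of the no-DLT path, not a contradiction.

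**Conclusion.** The concern holds in a limited form. Followed as published, the rule can release level 4 before toxicity in patients 1–3 is fully observable, and LVEF decline is the clear blind spot. With a flat 20% rate and uniform onset, level 4 is reached at patient 4 in 55%, 65% or 82% of trials at 60-, 30- or 14-day spacing, against 51% with full observation. The excess disappears at 90 days or more.

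A reader might infer that patients in this trial were in fact escalated blind. The article gives neither accrual intervals nor the full protocol's rules, so that cannot be concluded. Nor does the point establish that a 90-day wait at every step is the only sound choice; that is a trade-off between time and residual late risk. The change is worth making, with medium confidence, because the step with least prior human experience has the least protection.

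**What to change.** In the sample size section:

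- Define the DLT and its window.
- Require the preceding patient to complete that window without a DLT before each escalation, at least before levels 3 and 4.
- Allow an acute window shorter than 90 days if it is justified and either an LVEF reading within it is used (an interim echocardiogram or one already available) or the remaining late risk is stated. Later events should still feed the stay and de-escalate rules.
- Remove or qualify the sentence that escalating too quickly is very unlikely.

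In the ethics and safety section, tie the existing DSMB meeting after subject 2 to the release of level 3, and require a review before first use of level 4.

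**Cost.** One added DSMB review, and calendar time only where accrual is faster than the window. At 30-day spacing patient 4 arrives on day 3 × 30 = 90. A 30-day window then adds nothing, but also changes nothing. A 90-day window before every step moves patient 4 to day 3 × 90 = 270, which adds 180 days. Applied only before levels 3 and 4, it gives day 30 + 90 + 90 = 210, which adds 120 days. At 14-day spacing, a 30-day window delays patient 4 from day 42 to day 90 and, in the flat 20% illustration, lowers 82% to 65%. Delays are longer after a DLT.

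If the full protocol already sets a window, a sentence stating it is enough. If escalation is already complete, apply the window to the remaining stay and de-escalate decisions.
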